### How will blinding be achieved {24b}

Individuals blinded to the intervention allocation (e.g. the chief investigator) will not have access to information related to participants’ group assignment, achieved via the role-based access in REDCap.

### Procedure for unblinding if needed {24c}

In the event of a serious adverse event, the research team will discuss the necessity, risk, and benefits of unblinding. If needed, the chief investigator will be unblinded, and the study coordinator will provide group allocation and other necessary information for investigation. No other participants’ allocation will be unblinded.

## Data collection and management

### Plans for assessment and collection of outcomes {25a}

Data will be collected, using validated questionnaires (see the “Outcomes {16}” section), via REDCap [27, 28] hosted on Monash University secure computing facilities. All questionnaires will be completed online via the REDCap system. Participants will be sent a unique participant access link to the questionnaires at the pre-specified assessment timepoints. To support the completeness of data, variables will be “required” to be entered by REDCap such that participants cannot move to the next page until all items are completed. Where data is missing or insufficient, the research team may contact the participant via email or phone to complete the remaining data. For participant screening calls, all researchers will be trained by [name] to promote reliability.

### Plans to promote participant retention and complete follow-up {25b}

Participants will receive at least three e-mail reminders to complete follow-up data collection. If no response is received via e-mail, at least one text message reminder will be sent. Participants will receive a gift card for each survey completed with $15AUD awarded for each of the first four surveys (T1, T2, T3, T4) and $20AUD for each of the last two surveys (T5, T6). Participants will also receive a study newsletter update at various points throughout the study to assist with retention.

### Data management {26}

Participants will complete online questionnaires through REDCap, hosted on Monash University secure computing facilities, with data backup handled by Monash University. Participant identifiable information (e.g. names, address) will only be stored in REDCap, which has role-based secure access and dual-authentication login. Outside REDCap participants will only be identified using a numeric ID. All interview and intervention data will be stored on a secure Monash server. The data collected will be retained for a minimum of 15 years. No more than 7 years after the publication, data will be de-identified, and the de-identified database will be made publicly available.

### Confidentiality {33}

Identifiable information will not be shared with anyone outside the research team except in the following context: (i) Participants have the right to access the information collected and stored by researchers about themselves; (ii) a research team member believes that there is a potential risk or danger posed to a participant or someone else, and their contact details may be provided to support services; or (iii) data may also be shared if required by law. All data is collected and stored in REDCap, hosted on Monash University secure computing facilities, with data backup handled by Monash University. Audio and video recordings will be stored on a secure Monash University drive, which can only be accessed by the research team using dual-authentication login. Identifying information will not be reported in publications.

## Statistical methods

### Statistical methods for primary and secondary outcomes {27a}, {27b} and {27c}

A detailed descriptive profile will be created for all outcomes, intervention conditions, sample characteristics, and intervention adherence. Descriptive statistics will be as follows: (1) For continuous variables that are approximately normally distributed without outliers: mean and standard deviation; (2) for continuous variables that are not normally distributed or have outliers: median and interquartile range; and (3) for discrete variables: frequency and percentage.

We will report the frequency and percent of participants who completed each timepoint and who have missing data at each timepoint. Adverse event frequency and type will be reported with frequencies and percentages. We will compare the proportion of withdrawn or missing participants at each timepoint and the proportion of adverse events by condition using chi-squared tests.

#### Effectiveness for Aim 1

To test aim 1, which is ISI (primary) and SRI (secondary) will be lower in the Healthy Sleep Program than the Control condition, we will use regression analyses. Analyses will be intention to treat, with participants analysed in the condition to which they were assigned regardless of actual intervention receipt. Significance is set at *α* = 0.01, two-tailed. We will calculate the expected raw difference in outcomes between treatment and control with 95% confidence intervals, along with the standardised difference to measure the effect size. All effectiveness analyses for Aim 1 will be conducted in R.

The dual primary (ISI at pregnancy and postpartum) and two secondary (SRI at pregnancy and postpartum) outcomes will be used as described previously (see “Outcomes {16}”) with the outcomes treated as continuous variables. Analyses will be separate regressions for each outcome, with the outcome as the dependent variable. Treatment condition will be dummy coded (Healthy Sleep Program = 1, sleep hygiene education = 0) and included as the focal predictor. The outcome measure at baseline (T1) will be included as a covariate. That is, ISI at T1 will be included for both ISI primary outcomes, and the SRI at T1 will be included for both SRI secondary outcomes. Randomisation strata will be fully crossed and dummy coded, and these dummy codes will be included as covariates [61]. The method selected for statistical inference for the main analyses will depend on features of the data.

If outcome data are missing, we will use multiple imputation through chained equations (MICE, [63]) based on predictive mean matching (PMM; [64]). We will generate 100 imputed datasets.

*Second*, if model residuals are approximately normally distributed, we will use normal theory-based standard errors to calculate confidence intervals and *p*-values. If model residuals are not normally distributed, we will use a nonparametric bootstrap with percentile-based confidence intervals based on 20,000 bootstrap samples. In this case, in addition to reporting 95% confidence intervals, we will use the 99% bootstrap percentile intervals to determine statistical significance based on whether or not the interval includes 0. The distribution of model residuals will be determined by fitting a linear regression model and creating a density plot of the residuals and a Q-Q plot of the observed residuals against a normal distribution.

*Third*, if there are no outliers in the model residuals, we will use regular linear regression. If there are outliers in the model residuals, we will use quantile regression and use a median (50th percentile) estimator. Outliers in the residuals will be determined by fitting a linear regression model, extracting the residuals and creating a density and rug plot.

The above choices will be combined as necessary based on the data. For example, if outcome data are missing, the residuals demonstrate non-normality and there are outliers, we would use quantile regression, non-parametric bootstrapping and multiple imputation. In cases where we use both bootstrapping and multiple imputation, we will use the approach of bootstrapping in the outer loop and then using imputation in the inner loop [65]. That is, for each of 20,000 bootstrap samples, we will use MICE with PMM to generate a single imputed dataset with added noise reflecting the uncertainty of the imputation, resulting in a total of 20,000 datasets that are both bootstrapped and imputed. This was selected as a simulation study demonstrated that while it is computationally demanding, it provides the best validity [65].

We will conduct and report sensitivity analyses. *First*, we will conduct a complier average causal effect analysis, which estimates the impact of an intervention in the population subgroup that complies with its assigned treatment, which will illuminate the intervention effect on women who received the minimum recommended amount of intervention. *Second*, we will conduct controlled multiple imputation, with an offset, δ, added to the imputed missing outcome data [66]. Specifically, we will vary *δ* assuming that participants who dropout and have missing data experience worse-than-expected outcomes. That is, a non-random pattern whereby people are more likely to dropout or have a missing outcome when the outcome is worse. We will vary the magnitude of *δ* and report treatment estimates across the range of *δ* values.

We will conduct two secondary analyses. First, we will test a condition × recruitment source interaction to assess intervention effect heterogeneity across sources. Second, we will conduct linear mixed models for ISI and SRI using scores at each individual timepoint to compare trajectories of insomnia and daytime symptoms between conditions. Protocol deviations will be documented, and sensitivity analyses will be carried out, if necessary, to examine whether findings hold with or without participants with deviations.

#### Economic evaluation for Aim 2

Cost-effectiveness and cost-utility analyses will be conducted from a societal perspective, summarising the health and productivity effects of the intervention during the trial period. Usual care is selected as the comparator to directly inform treatment and funding decisions. Direct costs of the active control condition will be excluded from analyses, with estimates of treatment effects for primary and secondary outcomes interpreted as conservative relative to usual care.

Primary and secondary outcomes for the economic evaluation are designed to capture hypothesised health gains during pregnancy for the pregnant participant and for the birthing parent and infant during the postpartum period. The primary outcome for the economic evaluation will be total QALYs in the birthing parent and infant from baseline to 24 months postpartum. For the birthing parent, total QALYs from baseline to 24 months postpartum will be calculated based on AQoL-4D [31] index scores at T1 to T6 in the main analysis and based on PROMIS-Pref (PROPr) index [32, 67] scores at T1 to T6 in sensitivity analyses. For infants, total QALYs from birth to 24 months will be calculated based on parent completion of the IQI at T3–T6 [36, 37]. The IQI is suitable for calculating QALYs in infants (0–12 months) [37], with coverage of seven domains of infant quality of life: sleeping, feeding, breathing, stooling/poo, mood, skin, and interaction.

The secondary outcome for the economic evaluation will be the primary clinical outcome during the postpartum period (average ISI during the postpartum period), representing overall symptom burden for the birthing parent and infant. Treatment effects with respect to QALYs will then be estimated using one-part generalised linear models (GLM), controlling for index scores at baseline and specifying appropriate variance and link functions [68].

Total cost per birthing parent–infant dyad will be calculated based on (i) per dyad cost of the intervention and usual care conditions, (ii) birthing parent self-report of health service utilisation for the birthing parent at T1 to T6 and for the infant at T3–T6 and (iii) productivity and activity impairment costs related to insomnia symptoms in the birthing parent during the trial period based on WPAI (insomnia) data at T1 to T6 [38]. Treatment effects with respect to total cost will be estimated using one-part GLM models with gamma variance function and a log link (rather than transformed ordinary least squares or two-part models [69]), controlling for birthing parent characteristics at baseline. Results will be expressed as (1) cost per QALY gained and (2) cost per point improvement on the primary clinical outcome. We will summarise sampling error and parameter uncertainty using the bootstrap acceptability method to calculate confidence intervals and generate cost-effectiveness acceptability curves [68].

#### Implementation evaluation for Aim 3

A subsample of randomised participants will be invited to take part in qualitative interviews to allow for exploration and analysis of the implementation potential of the Healthy Sleep Program. Additionally, clinicians who have delivered the intervention as well as perinatal professionals who routinely work with gestational parents (e.g. obstetricians and gynaecologists, general practitioners, midwives, psychologists) will be invited to participate in interviews.

The interviews will be semi-structured and aim to explore the barriers, enablers and contextual factors perceived to influence the sustainable implementation of the program. An interview guide with questions and prompts informed by the TDF [40] and PRISM [41] will guide the discussion. Interviews will be audio recorded and transcribed verbatim through a transcription service and/or by members of the research team. Transcripts will be imported into NVivo software [70] to manage the data and facilitate analysis. The interview transcripts with participants and their partners, treating clinicians and perinatal professionals will be analysed using thematic analysis to identify the factors perceived to influence the sustainable implementation of the Healthy Sleep Program. These factors will then be thematically mapped to the domains of the TDF and PRISM [71] to inform the design of implementation strategies to support wider scale-up and spread if shown to be clinically effective and cost-effective.

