### Sample size {19}

Sample size calculations for the present trial were informed by statistical, empirical, and clinical considerations, given cautions on basing power solely on pilot data [59]. Factors considered were as follows: (1) In a previous trial [21], Cohen’s d effect sizes for ISI and sleep-related impairment in women with baseline elevated ISI (> 7) ranged from 0.43 to 1.15. (2) Trial investigators with clinical experience discussed the smallest meaningful effect and identified a Cohen’s d = 0.40. (3) We calculated bootstrap confidence intervals for Cohen’s d from the previous trial data. Results showed that in > 75% of the time, the pilot effect size was Cohen’s d > 0.40, bolstering confidence that this clinically meaningful effect is highly plausible from our intervention.

For the effectiveness component of this trial, there are two primary outcomes (ISI at T2 and average ISI across T3–T5) and two secondary outcomes (SRI at T2 and average SRI across T3–T5) for a total of four hypothesis tests across primary and secondary outcomes. A Bonferroni correction for four tests would be *α* = 0.05/4 = 0.0125. We rounded down and conservatively set *α* = 0.01, two-tailed to adjust for multiple comparisons.

Planned primary and secondary analyses are four linear regression analyses, one for each outcome. Collectively, the models will have the following parameters estimated: 1 for the intercept, 1 for covarying for the outcome at baseline, 1 for the dummy-coded treatment condition, and 15 for the dummy-coded strata (see the “Sequence generation {21a} and {21b}” section for all 16 unique strata) resulting in a total of 18 estimated coefficients. For the pilot and for identifying a clinically important difference, we used Cohen’s d effect size. However, analyses are linear regressions to allow for covariates, so for power analyses, we translated Cohen’s *d* = 0.40 to a Cohen’s f2 of 0.04 using Cohen’s formula [60]:$${f}^{2}={\left(\frac{d}{2}\right)}^{2}$$

We used the pwr.f2.test() function from the R package pwr to calculate the required sample size for the following conditions:Two-tailed *α* = 0.01.One numerator degree of freedom, testing the dummy-coded treatment condition85% power10% dropout (90% retained)18 degrees of freedom used up in the regression models

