A further sample size consideration is the stratified randomisation. We have 16 total strata (see the “Sequence generation {21a} and {21b}” section for details). A rule of thumb [61] for stratified randomisation using permuted blocks is that the number of strata should be no more than N/(4 × block size). As we are using a big stick design (BSD) for randomisation with maximally tolerated imbalance (MTI) = 2, the block size approach does not directly apply. However, a *MTI* = 2 for a two-group design yields the same possible maximum imbalance as permuted blocks with block size *B* = 4. Using this rule of thumb gives us a minimum required sample size to prevent overstratification of *N* = 16 × 16 = 256. Power analyses showed that a sample size of *N* = 384 provides ≥ 85% power to detect a Cohen’s *d* = 0.40 (Cohen’s f2 = 0.04) with two-tailed *α* = 0.01 to account for multiple comparisons and the outcome variable at baseline and all strata included as covariates. This also exceeds the minimum sample size needed for 16 strata. Thus, the final planned sample size was *N* = 384.

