## Assignment of interventions: blinding

### Who will be blinded {24a}

Given the nature of the interventions, it is not possible for participants to be blind to their treatment allocation, but the condition pseudonyms “Group A” and “Group B” are used to avoid bias. As randomisation is completed by the research team and is necessary for administrative purposes, the study coordinator, research assistants, and clinicians will not be blinded to the group allocation. The chief investigator will be blinded to the group allocation except in exceptional circumstances where the risk to participants outweighs the benefit of blinding, such as evaluating a serious adverse event. Statisticians will not be blind to the condition in order to facilitate the conduction of statistical analysis.

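### A by-eye outlier check can replace the powered mean difference with a median difference in any of the four main analyses; the stated 85% power then holds only if residuals are heavy-tailed

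*Protocol article*

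**What the plan says.** All references are to the protocol article.

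- **Sample size {19}** bases power on a mean comparison: "Planned primary and secondary analyses are four linear regression analyses, one for each outcome". The effect is set by clinical judgement ("Trial investigators with clinical experience discussed the smallest meaningful effect and identified a Cohen’s d = 0.40") and then converted: "we translated Cohen’s *d* = 0.40 to a Cohen’s f2 of 0.04". The result is that N = 384 "provides ≥ 85% power to detect a Cohen’s *d* = 0.40". The later increase to 495 keeps the same analysed number, 346, at 70% completion.
- **Statistical methods {27a}, {27b} and {27c}, Effectiveness for Aim 1**, promises the expected raw difference between arms, which is a mean. The test level is given as: "Significance is set at *α* = 0.01, two-tailed". The section adds that the inference method for the main analyses will depend on features of the data.
- **The same section, third step:** "If there are outliers in the model residuals, we will use quantile regression and use a median (50th percentile) estimator". The trigger is described as follows: "Outliers in the residuals will be determined by fitting a linear regression model, extracting the residuals and creating a density and rug plot". No cut-off is given.
- **Who will be blinded {24a}:** "Statisticians will not be blind to the condition in order to facilitate the conduction of statistical analysis".
- **Sensitivity analyses, same section:** a complier average causal effect, delta-adjusted imputation, and protocol deviations if needed. Reporting the estimator not selected is not listed.
- **Protocol and statistical analysis plan {5}** states that the analysis plan is contained in this article.

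**The concern.** Linear regression estimates a difference in means, and median regression a difference in conditional medians. Unless the treatment shifts the whole outcome distribution equally, these are different quantities. Under the rule as written, which one a primary endpoint reports depends on how a plot strikes the analyst. The choice is made outcome by outcome, so the pregnancy endpoint could report a mean and the postpartum endpoint a median. Average postpartum ISI also feeds the cost per point improvement in the economic evaluation, where a mean effect is the natural input.

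Three features make this more than a technicality:

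- The sample size was derived for one estimator only. Median regression is less efficient when residuals are close to normal.
- The trigger is not operational. Two competent statisticians could look at the same plot and disagree, and the one who decides is not blind to arm.
- The alternative result need not appear in the report, so a reader could not see whether the choice mattered.

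For the ISI outcomes the gain from the switch is also limited. The total is bounded at 0-28, so an extreme residual is a valid score. That argument does not carry over to the two SRI outcomes, which are T-scores.

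**Working it through.** **Inputs from the protocol.** Two-sided alpha 0.01; d = 0.40; f2 = (0.40/2)^2 = 0.04; one numerator degree of freedom; 18 coefficients; 85% power; 10% dropout; later 346/0.70. Equal allocation is implied by the two-arm big stick design but is not stated as a ratio.

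**Step 1: reproduce the stated figure.** The noncentral F calculation uses noncentrality lambda = f2 x (u + v + 1), with u = 1. Solving for 85% power gives v = 327.5.
- n = 327.5 + 18 = 345.5, that is 346 analysed.
- 345.5/0.90 = 383.9, that is 384. The protocol's N reproduces.
- At n = 346, v = 328 and lambda = 0.04 x 330 = 13.2. Power is 85.1%.
- 346/0.70 = 494.3, that is 495, also as stated.

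**Step 2: power after the switch.** In large samples, multiply lambda by the efficiency of the median relative to the mean, ARE = 4 x f(0)^2 x sigma^2, where f(0) is the residual density at its median and sigma^2 the residual variance. For normal residuals ARE = 2/pi = 0.637 and lambda = 13.2 x 0.637 = 8.4. For 5% contamination (5% of residuals from a normal with three times the SD), f(0) = (0.95 + 0.05/3) x 0.3989 = 0.3856 and sigma^2 = 0.95 + 0.05 x 9 = 1.40, so ARE = 4 x 0.3856^2 x 1.40 = 0.83.

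| Residual shape (assumed) | ARE | Median regression power, n = 346 |
|---|---|---|
| Normal | 0.64 | 62% |
| 5% at three times the SD | 0.83 | 77% |
| t, 5 df | 0.96 | 83% |
| 10% at three times the SD | 1.00 | 85% |
| t, 4 df | 1.125 | 90% |
| Laplace | 2.00 | 99% |

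For normal residuals a plain normal approximation gives a z value of 0.40 x sqrt(346/4) x sqrt(0.637) - 2.576 = 0.39, or 65%. Hence 62-65%.

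**Step 3: simulation with baseline and 15 strata dummies (n = 346, 600 runs per shape).** Linear against median regression: normal 86% and 68%; 5% contamination 84% and 79%; t with 5 df 86% and 82%. The median figures are somewhat optimistic, because the software's default standard error for median regression rejected in 2.5% of null runs at a nominal 1%. A second simulation used rounded ISI scores bounded at 0-28, with assumed mean 10 and residual SD 4.5, a baseline covariate but no strata, and 500 runs per shape. It gave 88% and 67% for right-skewed residuals.

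**Step 4: can well-behaved data trigger the switch?** For 346 exactly normal residuals, the chance of at least one beyond k SD is 1 - (1 - 2 x P(Z > k))^346. This is 91% at the usual boxplot fences (k = 2.698), 61% at k = 3 and 15% at k = 3.5. The protocol names no k, so the trigger rate is unknown within a wide range.

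**Step 5: type I error.** Simulation of two arms with normal data, n = 346, no covariates, the median's standard error from the known density, and 40,000 runs. Switching to the median whenever any residual exceeded 3 SD rejected in 0.92% of null trials at nominal 1%. Picking the more favourable of the two tests rejected in about 1.6%. A repeat run gave 1.03% and 1.76%.

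**The case against.** Several points on the other side have force.

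- **The rule is written down in advance and aims at robustness.** True, but its trigger is not defined. Prespecification protects only if the rule can be applied without judgement.
- **The power loss depends on residual shape.** A reader might infer that the switch always cuts 85% to about 60-70%. The documents do not support that. They give no residual distribution, and for the heavy tails the rule is meant for, the loss shrinks or reverses. The low figures apply when stray points in near-normal data, or right skew, set off the switch.
- **346 is the planning floor for the postpartum endpoint.** Completion at T2 to T4 was 74-84%. Applied to 495 at T2, this gives 495 x 0.74 = 366 to 495 x 0.84 = 416. Under normality, power is then 87-92% for the mean and 65-73% for the median. The gap narrows slightly but remains.
- **Units of d.** If d = 0.40 is in raw SD units and the baseline correlation is 0.5 (an assumption), power is 94% for the mean and 77% for the median under normality. Both rise, and the ordering is unchanged.
- **Type I error.** A reader might infer that the switch inflates it. The rule selects on residual plots, not on p-values, and switching on residuals showed no inflation. Inflation needs someone to see both tests and choose, which the plan does not describe.
- **Unblinding.** The plots described are of pooled residuals, with no display by arm, so knowing the allocation matters less than it first seems. It still leaves a judgement call open to question.

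**Conclusion.** The point stands in conditional form. The main analysis of each of the four outcomes can move from a mean to a median difference on a visual judgement without a cut-off. That contradicts both the basis of the sample size and the promised expected difference, and the estimator not chosen need not be reported. At 346 analysed, with d in residual SD units and two-sided alpha 0.01, the 85% for linear regression becomes 62-65% for normal residuals, 76-77% with 5% contamination and 83% for t with 5 df. It reaches 85% or more only for heavier tails. Which figure applies cannot be determined from the protocol. No inflation of type I error follows from the rule itself; about 1.6% instead of 1% would arise only if the better of the two tests were picked. The defect lies in the undefined estimand and in power that is no longer assured.

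**What to change.** Delete the outlier branch in Effectiveness for Aim 1. State that the primary analysis for all four outcomes is the adjusted mean difference from linear regression, whatever the residuals look like. Fix the inference method in advance, within multiple imputation: either heteroscedasticity-robust standard errors or the bootstrap the section already describes, so that no choice depends on plots. Name median regression as a sensitivity analysis that is always reported beside the primary result for every outcome.

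This needs wording only. No new data or participants are required, follow-up is planned to about March 2027, and the 85% at 346 analysed is kept. The downside is some loss of efficiency if residuals turn out very heavy-tailed: for Laplace residuals the median would have 99% power at the same effect size, where linear regression has about 85%. Showing the median result alongside lets a reader see whether that matters.

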#### Updated increased sample size

When recruitment of the proposed sample size (*N* = 384) was complete, attrition and completeness of data were considered to assess the appropriateness of the sample size. Completion rates for T2, T3, and T4 varied between 74% and 84%, which was lower than the anticipated 90%. To account for this increased attrition, an increased sample size was required. The additional participant calculation is based on the following: If 70% of the sample completes at least 2 postpartum timepoints, a sample of 346/0.70 = 495 is needed; this is 111 more than planned. Thus, an increased proposed sample size of *N* = 495 is needed to account for potential impacts of attrition.

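### If outcomes are missing and residuals look non-normal, one imputation per bootstrap resample with percentile limits gives over-wide intervals: at 30% missing, the 0.01 test runs at about 0.003 and power is about 75%, not 85%

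*Protocol article*

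**What the plan says.** The subsection on effectiveness for Aim 1 (Statistical methods {27a}, {27b} and {27c}) sets the test level: "Significance is set at *α* = 0.01, two-tailed". Inference then depends on the data.

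- Missing outcomes are handled by chained equations with predictive mean matching (PMM) and 100 imputed datasets. If residuals look approximately normal, normal-theory standard errors are used.
- If residuals do not look normal, a percentile bootstrap with 20,000 samples replaces the normal theory, and "we will use the 99% bootstrap percentile intervals to determine statistical significance based on whether or not the interval includes 0".
- If outcomes are missing as well, bootstrapping is the outer loop and imputation the inner one: "for each of 20,000 bootstrap samples, we will use MICE with PMM to generate a single imputed dataset with added noise". The text does not average imputations within a resample or remove imputation noise from the limits. It supports the choice by citing a simulation study.

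The sample size section says that the planned size "provides ≥ 85% power to detect" d = 0.40. The updated sample size section then allows for attrition: "If 70% of the sample completes at least 2 postpartum timepoints, a sample of 346/0.70 = 495 is needed".

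**The concern.** An estimate from a resample imputed once varies for two reasons. One is the sampling variability of the multiple-imputation estimate, which already includes the price of the missing data. The other is the luck of one random imputation. The centre of the 20,000 estimates averages that luck away, but the 0.5th and 99.5th percentiles keep it in full. The limits are therefore wider than the uncertainty of the estimate they surround.

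Three things are at stake when this branch is used. The primary decision rule no longer has its stated level of 0.01. Power falls below target when missingness is near the allowance that justified adding 111 participants. And the same data would be tested at about 0.01 or at a stricter level depending on a visual reading of a residual plot, made by statisticians who are not blinded (section {24a}).

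**Working it through.** **Inputs.** Two-sided α = 0.01, 85% power, one numerator degree of freedom, d = 0.40 converted "to a Cohen’s f2 of 0.04 using Cohen’s formula", and a model "resulting in a total of 18 estimated coefficients" (section {19}). N = 495 with 70% having the postpartum endpoint, and completion of 74% to 84% at T2 to T4, that is 16% to 26% missing (updated sample size section). Equal allocation is assumed.

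**The plan's own figure.** The noncentral F calculation behind pwr.f2.test, with noncentrality f²(v + 2), needs v = 327.5 residual degrees of freedom. Adding 18 gives n = 345.5, or 346. Then 346/0.90 = 384.4 and 346/0.70 = 494.3, in line with the stated 384 and 495. Power at 346 is 85.1%.

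**Variance.** Let W be the complete-data variance, B the between-imputation variance and T = W + B the variance of the multiple-imputation estimate. With outcomes missing in a fraction m and no auxiliary information, B = mT. One proper imputation per resample gives estimates with variance T + B = (1 + m)T, while the centre has variance of about T. Hence:

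- width ratio r = √(1 + m)
- actual level = 2[1 − Φ(2.576 r)]
- coverage of a nominal 95% interval = 2Φ(1.96 r) − 1
- power = Φ(2.576 + z − 2.576 r), where z is the normal quantile of the power without the excess width (1.036 for 85%)

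**At m = 0.30.** r = √1.30 = 1.140. The level is 2[1 − Φ(2.937)] = 0.0033. Coverage is 97.5%. Power is Φ(3.612 − 2.937) = Φ(0.675) = 75%. If the added noise is residual noise only, with no draw of the imputation-model parameters, B = m(1 − m)T. Then r = √1.21 = 1.10, the level is 0.0046 and power is 78%.

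**At the observed missingness with N = 495.** The analysable number rises as m falls, so the starting power must be recomputed each time. The ranges cover two conventions for the noncentrality, f²(v + 2) and f²n.

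| Missing | Analysable | r | Actual level | Power, correct width | Power, plan's rule |
|---|---|---|---|---|---|
| 16% | 416 | 1.077 | 0.0055 | 92-93% | 89-90% |
| 20% | 396 | 1.095 | 0.0048 | 90-92% | 86-87% |
| 26% | 366 | 1.123 | 0.0038 | 88-89% | 80-82% |

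**Simulation check.** Settings: N = 495, 30% of outcomes missing completely at random, 16 strata plus baseline and treatment, PMM with 5 donors, 400 resamples per trial, 600 to 1,000 trials per setting.

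- The bootstrap SD was 1.17 times the Rubin standard error and 1.16 to 1.21 times the empirical SD of the estimate.
- Under no effect, the 99% percentile rule rejected in 0.4% (normal errors) and 0.5% (skewed errors) of trials. Rubin pooling rejected in 0.7% and 1.3%.
- With an effect of 0.40 and normal errors, the percentile rule had power of 77%, against 87% for Rubin pooling.

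With only 400 resamples the percentile limits are slightly narrow. Using 2.576 bootstrap SDs instead gave power of 74.5% and rejection under no effect of 0.1% to 0.3%.

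**The case against.** Much of the case on the other side stands.

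- **The rule is conditional.** It applies only if outcomes are missing and residuals are judged non-normal. A reader might infer that the trial as a whole tests at 0.003 with 75% power. The document does not support that: the normal-residual branch uses 100 imputations and is unaffected, and nothing shows which branch will be used.
- **30% is an allowance.** The text is hypothetical ("If 70% of the sample completes at least 2 postpartum timepoints") and concerns the postpartum endpoint only. A reader might hold starting power at 85% for lower missingness and conclude, for example, that 20% missing gives about 79%. That is wrong for N = 495: 396 are then analysable and power stays at about 86-87%, still at target.
- **Auxiliary data shrink the effect.** A participant whose postpartum endpoint is missing may still have one postpartum score or the T2 score. If such scores cut the fraction of missing information to, say, 15%, r is 1.072 and the level 0.0057. The article does not give the imputation model, which the fuller plan may specify.
- **The 85% may be cautious.** The conversion takes no credit for baseline ISI. If d = 0.40 is on the raw SD scale and the baseline-outcome correlation is assumed to be 0.4, f² = 0.04/(1 − 0.16) = 0.0476. Power at 30% missing is then about 85-87% even with the wide interval, but it would be about 92-93% without it. The loss remains.
- **The error is conservative.** A reader might infer a risk of false-positive findings. There is none from this source: the actual level is below 0.01 and intervals over-cover.

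The cited simulation study is not at hand and was not used. Coverage at or above nominal would in any case be compatible with intervals that are too wide.

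**Conclusion.** The point holds in conditional form. In the branch with missing outcomes and non-normal residuals, single imputation within each resample followed by percentile limits counts between-imputation variance twice. For linear regression with little auxiliary information, intervals are too wide by about √(1 + fraction of missing information).

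At the 30% allowance this means 14% excess width, an actual level of about 0.003, about 97.5% coverage of nominal 95% intervals, and power of about 75% instead of 85%. At the 16% to 26% seen so far, the loss is about 3 to 8 percentage points, and power falls below 85% only towards the upper end of that range.

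The figures rest on equating the fraction of missing information with the fraction missing, on proper imputation, and on linear regression. The combination with median regression, which is the protocol's own worked example, was not computed. Because the error is conservative, conditional and correctable before final analysis, this is something that should be fixed; it does not invalidate the trial.

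**What to change.** Amend the text for this branch before final analysis, in one of these ways:

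1. Use the 100 imputations already planned, with heteroscedasticity-robust standard errors combined by Rubin's rules. This is the simplest option for linear regression and brings the two residual branches into line.
2. If the bootstrap is kept, average several imputations within each resample before taking percentiles. With 10 per resample the variance is T + B/10. At 30% missing, r = √1.03 = 1.015, the level is 0.0089 and power is about 84%.
3. Use two imputations per resample with a variance-component interval that removes the between-imputation part.

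The text should also say which interval applies when median regression is used, since option 1 as worded covers linear regression only.

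The cost is wording and code. Option 2 has a downside: within the same 20,000 imputed datasets, 10 per resample leaves 2,000 resamples and about 2,000 × 0.005 = 10 draws beyond each 99% limit, against 100 now. The limits would be noisier. Keeping 20,000 resamples would need 200,000 imputed datasets, so more computing time.
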